## Abstract

**Background/Objectives**: Despite progress in secondary prevention, people with chronic coronary syndrome (CCS) still face a residual risk of ischemic events. Antithrombotic therapy reduces this risk and helps stabilize chronic cardiovascular disease. Studies have shown that combining low-dose rivaroxaban with aspirin—an approach called dual-pathway inhibition (DPI)—can lower this risk and reduce major adverse cardiovascular events (MACEs). However, researchers have not yet gathered enough real-world data to confirm the efficacy and safety of this strategy. The DUTCH CCS registry aims to collect real-world data on how effective and safe low-dose rivaroxaban combined with aspirin is for patients with CCS in The Netherlands. The study aims to provide insights into the outcomes, benefits, and risks of DPI in a real-world setting, beyond the scope of controlled clinical trials. **Methods**: The DUTCH CCS registry operates as a national, multicenter, prospective observational study. It enrolls 1000 patients with CCS who receive rivaroxaban (2.5 mg twice daily) and aspirin (80 mg or 100 mg once daily). The study targets individuals at high ischemic risk due to coronary artery disease (CAD) and follows a single-arm design. Researchers will measure the primary efficacy endpoint by tracking MACEs, clinically driven coronary, peripheral, or carotid revascularization, and stent thrombosis over one year. They will assess the primary safety endpoint by recording major bleeding events at one year. The team will collect data at both 3-month and 1-year follow-ups. **Conclusions**: As an observational study, this registry is not designed to establish causality. However, it seeks to improve our understanding of how DPI performs in real-world secondary prevention for CCS patients. The results may help update treatment guidelines and inform clinical decisions in everyday practice.

## 1. Introduction

Chronic coronary syndrome (CCS) still poses a significant risk for major adverse cardiovascular events (MACEs). A patient’s clinical history—such as previous myocardial ischemia, obstructive coronary artery disease (CAD), and cardiovascular risk factors—strongly influences the incidence of these events. The REACH (Reduction of Atherothrombosis for Continued Health) registry reports 4-year MACE rates of 18.3% in patients with a history of ischemia, 12.2% in those with stable CAD, and 9.1% in patients with risk factors alone [1]. These data highlight the substantial residual risk in CCS and emphasize the need for continued vigilance and optimized therapy.

Clinicians typically use long-term single antiplatelet therapy with aspirin as the standard treatment for CCS. This approach reduces MACEs by about 22% annually. Despite this benefit, many patients still face a high residual ischemic risk, which calls for more refined antithrombotic strategies [2,3].

Researchers believe that persistent thrombin generation, which can last for months after an acute coronary event, contributes to this ongoing risk by driving inflammation and atherosclerosis [4,5,6]. In response, multiple studies have tested anticoagulants in both acute coronary syndrome and CCS patients for secondary prevention [7].

Although vitamin K antagonists lower ischemic events, they also raise the risk of major bleeding, which limits their usefulness. In contrast, rivaroxaban—a direct oral anticoagulant—offers a more favorable safety profile. It works by selectively inhibiting coagulation pathways, reducing thrombin production, and limiting platelet activation [8,9,10].

The COMPASS trial tested low-dose rivaroxaban in patients with stable CAD [11]. In the trial, patients received either rivaroxaban 2.5 mg twice daily with aspirin or rivaroxaban 5 mg once daily alone. The combination therapy lowered the risk of MACEs by 24% compared to aspirin alone, mainly by reducing strokes. Rivaroxaban alone did not show additional benefit and had a similar bleeding profile to aspirin. Among high-risk patients—including those with multivessel CAD, diabetes, prior myocardial infarction (MI), peripheral artery disease (PAD), heart failure, or moderate kidney disease—the combination therapy led to even greater absolute risk reduction [12]. However, it also caused more major bleeding (3.1% vs. 1.9%).

The VOYAGER-PAD trial produced similar findings. In patients with PAD who underwent revascularization, rivaroxaban combined with aspirin reduced MACEs more effectively than aspirin alone [13].

Based on this evidence, the European Society of Cardiology guidelines recommend low-dose rivaroxaban for CCS patients who have completed twelve months of dual antiplatelet therapy (DAPT) without major bleeding and have no history of stroke or transient ischemic attack. This recommendation holds a Class IIa–IIb, Level A rating [14,15]. Clinicians should especially consider this strategy for patients with high thrombotic risk and acceptable bleeding risk. They may also apply it to patients with moderate thrombotic risk.

Although clinical trials have shown promising results, researchers still lack sufficient real-world data on low-dose rivaroxaban in high-risk CCS patients. To address this gap, the DUTCH CCS registry has been established. Moreover, randomized trials often exclude elderly, frail, or multi-morbid patients. This results in a paucity of real-world evidence on DPI’s net clinical benefit across broader populations. Our registry addresses this gap by evaluating DPI in a pragmatic clinical environment, with broader inclusion criteria reflective of contemporary cardiology practice.

This observational study focuses on Dutch patients with CCS who face a high risk of ischemic events but have a relatively low bleeding risk. The study evaluates the safety and effectiveness of DPI in routine clinical settings. We hypothesize that DPI improves clinical outcomes without significantly increasing bleeding, even under real-world conditions. Because the study includes a broader high-risk population and defines outcomes more broadly—including revascularization and stent thrombosis in addition to MACEs—we expect to observe a higher rate of ischemic events than reported in randomized trials.

## 2. Methods

### 2.1. Study Design

The DUTCH CCS registry is a nationwide, multicenter, prospective, observational, single-arm study involving 1000 CCS patients who are treated with rivaroxaban 2.5 mg twice daily in addition to aspirin 80–100 mg once daily. The study is conducted in twelve interventional cardiac centers, situated across various regions of The Netherlands. Investigators at Isala Hospital in Zwolle are responsible for the oversight and coordination of the registry and data management. Figure 1 presents the geographic locations and specific roles of the twelve participating study sites.

From December 2020 to May 2022, this registry has been enrolling consecutive adult patients (aged 18 years or older) who are diagnosed with CAD, exhibiting one or more of the following high-ischemic-risk features: (1) coexistence of PAD, (2) recurrent MI (subsequent to an initial MI), (3) diabetes mellitus, (4) chronic kidney disease (eGFR 30–59 mL/min/1.73 m^3^), (5) heart failure (with an ejection fraction ranging from ≥30% to 50%) and New York Heart Association (NYHA) class I or II, and/or (6) CHA_2_DS_2_-VASc score (greater than 3 for men or greater than 4 for women). Although patient recruitment was completed between December 2020 and May 2022, the study is designed as a prospective observational registry from the outset.

All data collection and follow-up procedures are conducted in real time, in accordance with a predefined protocol established prior to enrollment. While the current manuscript is written after data collection, the analysis is based on prospectively gathered data, consistent with the study’s original design and intention.

### 2.2. Ethics and Informed Consent

Ethical approval for the study was granted by the non-WMO (WMO = Medical Scientific Research Act) Advisory Committee of a recognized Ethics Committee on behalf of the DCRF (‘Dutch Clinical Research Foundation’) for all sites after reviewing the protocol, site-specific informed consent forms, and other requested documents. Under Dutch law, this classification applies to research that does not involve interventions or procedures beyond standard clinical practice. As our study is observational and does not involve additional risk or burden to participants, formal review by a medical ethics committee under the WMO was not required.

Before participation, the treating physician informs the patient orally and in writing about the scope and purpose, rights, duties, and possible risks/benefits of the registry in lay language. Written informed consent from the patient is a prerequisite to participate in the registry. To maintain confidentiality, patients are identified only by their identification code. All patients will also receive a patient information form.

All study-related information will be stored securely at the study site. All participant information will be stored in locked file cabinets in areas with limited access. All reports, collected data, and process and administrative forms will be identified by a coded identification number only to maintain participant confidentiality. All records that contain names or other personal identifiers, such as locator forms and informed consent forms, will be stored separately from study records, identified by code number. All local databases will be secured with password-protected access systems. The study findings will be disseminated via publication of peer-reviewed manuscripts.

The results will be published irrespective of whether the findings are positive or negative.

### 2.3. Study Population

Patients, both women and men, diagnosed with CAD enroll in the outpatient clinic following the treating physician’s decision to initiate treatment with rivaroxaban 2.5 mg twice daily, in combination with aspirin 80–100 mg once daily. Inclusion criteria apply to patients visiting the outpatient clinic from Q4 2020 to Q2 2022 who meet the specified requirements and provide written informed consent. The study diligently considers indications and contraindications in accordance with the local market authorization.

In alignment with the study’s objective to capture real-life data, the inclusion and exclusion criteria are less stringent compared to randomized settings (e.g., the COMPASS trial). This approach reflects the considerable diversity of our patients and the varying complexity of the medical cases encountered in everyday clinical practice.

### 2.4. Study Size

The DUTCH CCS registry is a prospective, observational, single-arm study designed for descriptive and exploratory analysis. The study aims to enroll 1000 patients with chronic coronary syndrome (CCS), treated with low-dose rivaroxaban in addition to aspirin. The target sample size reflects a balance between feasibility and the goal of generating clinically meaningful insights within the study’s timeframe. Enrollment will continue beyond 1000 patients if needed to compensate for a dropout rate exceeding 5%, ensuring that sufficient patients are available for 12-month follow-up.

Although no formal power calculation was performed, the sample size is expected to provide adequate precision to estimate event rates for major outcomes, including MACEs and major bleeding, with 95% confidence intervals. Expected event rates were informed by incidence proportions observed in the COMPASS trial. However, due to the shorter follow-up period in our study (12 months vs. 23 months in COMPASS), the incidence of similar endpoints is expected to be lower. Conversely, the broader definition of clinical outcomes in our registry—which includes not only conventional MACEs but also clinically indicated coronary, peripheral, or carotid revascularization and stent thrombosis—may lead to higher overall event rates.

Furthermore, although the patient population largely resembles that of COMPASS, we include patients with higher CHA_2_DS_2_-VASc scores, potentially increasing the observed number of ischemic events. Based on these factors, we estimate that most clinical endpoints will occur in 1% to 5% of patients, which allows for reasonably precise estimates of outcome frequencies in relevant subgroups.

To support interpretation and assess the robustness of our findings, we will conduct sensitivity analyses. These include stratified analyses by clinical risk factors (such as diabetes, PAD, or prior MI), comparisons based on narrow versus broader endpoint definitions, evaluation of patients with complete versus incomplete follow-up, and exploration of site-level variability. These analyses will contextualize the observed outcomes and help determine the consistency of results across different analytical assumptions, despite the absence of formal hypothesis testing.

### 2.5. Study Endpoints

The primary effectiveness endpoint is a composite of the following events at one year:Major adverse cardiac events (MACEs; composite of cardiovascular death, myocardial infarction (MI), or stroke);Clinically driven coronary, peripheral, or carotid revascularization;Stent thrombosis.

Clinically driven revascularization is defined as a de novo hospital admission that leads to revascularization (excluding planned or staged procedures). Definite or probable stent thrombosis is defined according to the Academic Research Consortium (ARC) criteria [16]. Myocardial infarction is defined according to the fourth universal MI criteria [17].

The primary safety endpoint is major bleeding during one year. These major bleeding complications are analyzed according to the International Society on Thrombosis and Haemostasis (ISTH) criteria as a composite of (1) fatal bleeding, (2) symptomatic bleeding into a critical organ (such as intracranial, intraspinal, intraocular, retroperitoneal, intra-articular or pericardial, or intramuscular with compartment syndrome), or (3) bleeding causing a fall in hemoglobin level of 2 g/dL (1.24 mmol/L) or more or leading to transfusion of two or more units of whole blood or red cells [18]. In addition, all bleeding events, including minor bleedings according to ISTH definitions, will be reported.

Secondary endpoints will be the following:Occurrence (and date) of stroke.Occurrence (and date) of MI.Occurrence (and date) of cardiovascular death.Occurrence (and date) of coronary revascularization procedures (PCI, CABG).Occurrence (and date) of peripheral revascularization procedures.Occurrence (and date) of carotid revascularization procedures.Occurrence (and date) of minor bleeding complications according to ISTH (clinically relevant bleeding that does not meet criteria for major bleeding and that requires any medical or surgical intervention to treat the bleeding).

A detailed overview of the primary endpoints is provided in Table 2.

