### 2.6. Data Collection and Follow-Up

The members of the study team prospectively gather data. During the baseline visit (T = 0), they collect historical data (demographic, laboratory—including parameters like hemoglobin, eGFR, and liver function—and clinical characteristics, including medication usage) from available medical records or through patient interviews if records are unavailable.

Primary and secondary endpoints are recorded at both 3-month and 1-year follow-up. The 3-month follow-up is conducted via telephone interview. Laboratory results are noted to the extent available within routine clinical practice, without performing additional study-related laboratory analyses. Patients are queried about adverse events, side effects of rivaroxaban, and any changes in their antithrombotic regimen (e.g., temporary cessation of aspirin, rivaroxaban, or both) and other medications. The time of final data collection is at one year, either through a face-to-face visit or via telephone contact (±30 days), or at 30 days in case of an early discontinuation of rivaroxaban therapy.

Potential reasons for premature study termination include consent withdrawal, loss to follow-up, or death of the patient. At this final observation, the patient’s condition and treatment assessment will be documented.

The treating physician determines the actual duration of treatment, which is not contingent on the initially intended treatment duration. In patients who permanently discontinue the combined treatment, discontinue rivaroxaban alone, or discontinue aspirin alone and who do not withdraw consent or experience a fatal adverse event during the observational period, the treating physician collects information on their survival status at the end of the study (i.e., 1-year ± 30 days after study inclusion).

A more detailed description of the variables collected during these visits is found in Table 3.

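### Cardiovascular death is the only general death endpoint, but after early rivaroxaban discontinuation the follow-up text conflicts and, on its narrower reading, gives no route to the cause of a late death

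*Protocol article*

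**What the plan says.** **Endpoints (Section 2.5, Table 2).** The MACE part of the primary composite is a "composite of cardiovascular death, myocardial infarction (MI), or stroke". The secondary list contains "Occurrence (and date) of cardiovascular death". Fatal bleeding enters only through the major-bleeding safety endpoint. All-cause death is neither a primary nor a secondary endpoint.

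**Follow-up (Section 2.6).** Three statements bear on patients who stop treatment:

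- The general rule: "Primary and secondary endpoints are recorded at both 3-month and 1-year follow-up".
- Final data collection is at one year, "or at 30 days in case of an early discontinuation of rivaroxaban therapy".
- A rule for the end of the study. It begins "In patients who permanently discontinue the combined treatment, discontinue rivaroxaban alone, or discontinue aspirin alone", is limited to those "who do not withdraw consent or experience a fatal adverse event during the observational period", and says that "the treating physician collects information on their survival status at the end of the study". It does not mention cause of death.

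The footnote to Table 3 lets adverse-event collection end 30 days after the last rivaroxaban, or at the end of observation.

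**Adjudication and analysis.** Section 3 has the clinical events committee adjudicate endpoint-related adverse events. Section 2.8 plans incidence proportions, exact confidence intervals and Kaplan–Meier estimates for the primary and secondary endpoints. Follow-up there runs to first event, loss to follow-up or the end of the year. Patients without an event are right-censored at last contact.

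**The concern.** A cause-specific death endpoint needs a cause for every death inside the analysis window. Survival status shows that a patient died, not why. If event collection closes 30 days after rivaroxaban is stopped and only survival status is sought at one year, a later death falls outside the adverse-event window and so outside the stated route to adjudication.

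Section 2.8 does not say how such a death is handled. It is not an event of a listed type, so it may be censored, and in the incidence proportions the patient may stand in the denominator as event-free. The study's main outputs are descriptive rates, so an undercount goes straight into the reported figure. Section 4 intends to contrast the findings with the reference trial and refers to net clinical benefit, so the rates will be read beyond the registry.

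**Working it through.** The article states no derived figure on this point, so there is nothing to reproduce. The check is a reading of the text followed by an estimate of the size under stated assumptions.

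**1. The text for a patient who stops rivaroxaban at month 4 and dies at month 9**

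| Statement | Consequence |
|---|---|
| Section 2.6, general rule | Endpoints recorded at one year, so cause should be obtained |
| Section 2.6, 30-day rule, with Table 3 footnote | Final data collection about month 5; the death is outside it |
| Section 2.6, survival-status rule | Death is found at one year; cause not named |
| Section 3 | Adjudication covers endpoint-related adverse events; a death outside the adverse-event window is not clearly one |
| Section 2.8 | No listed event recorded, so censoring is possible |

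The first row conflicts with the second and third, and nothing in the article says which governs.

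**2. Person-time with survival status only (narrower reading)**

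Inputs: one-year window and 30-day tail (Section 2.6). Assumptions, because the article gives neither figure: a fraction d of patients stops, with stop times uniform over the year, and d ranges from 10% to 25%.

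Mean time per stopper = (1 − 30/365)² / 2 = 0.9178² / 2 = 0.421 years.

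Share of first-year person-time = d × 0.421:

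- d = 10%: 4.2%
- d = 15%: 6.3%
- d = 25%: 10.5%

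**3. Deaths in that window per 1000 patients**

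Assumption: annual all-cause mortality m of 1.5–2%, the same hazard on and off treatment. Expected deaths = 1000 × m × d × 0.421.

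| | m = 1.5% | m = 2% |
|---|---|---|
| d = 10% | 0.63 | 0.84 |
| d = 25% | 1.58 | 2.11 |

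So roughly 1–2 deaths per 1000. If the hazard after stopping were three times as high, purely as an illustration, the range would be 3 × 0.63 = 1.9 to 3 × 2.11 = 6.3.

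**4. Against the expected counts**

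Section 2.4 expects most endpoints in 1% to 5% of 1000 patients, that is 10 to 50 events. The exact 95% confidence intervals are 0.48–1.83% for 10 events and 3.73–6.54% for 50.

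If all the affected deaths were cardiovascular, 0.63 to 2.11 deaths would be 6–21% of a count of 10 and 1–4% of a count of 50. In absolute terms this is about 0.06 to 0.21 percentage points, which is smaller than the sampling uncertainty. Unlike sampling error, though, it runs in one direction.

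**The case against.** The strongest answer is that Section 2.6 itself says all endpoints are recorded at one year, Section 2.8 runs the analysis period to the end of one-year follow-up, and stopping treatment is not among the listed reasons for premature study termination. On that reading, cause of death was sought in everyone. The case report form is not shown, and a condensed article's silence on one field is weak evidence that the field is absent. This stands to the extent that the defect is an unreconciled conflict, not a proven loss of data.

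A second answer is that, if collection does stop at 30 days, infarction, stroke, revascularization and major bleeding are lost too, and an all-cause death row repairs none of that. This is correct, and it is why reconciling the follow-up text comes first.

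Several stronger readings are tempting but not supported:

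- *Survival status is the sole one-year outcome in everyone who stops treatment.* The general recording rule says otherwise, and the 30-day cut-off is tied to rivaroxaban, so it does not clearly reach patients who stop aspirin alone.
- *Vital status is known for every patient.* Consent withdrawals are exempt from the check, and loss to follow-up remains possible.
- *Survival status will go unreported.* The article gives it no planned analysis but does not say this.
- *The gap makes the treatment look better.* An undercount lowers a descriptive rate, but the study has one arm and no formal test, and the article gives no data on deaths after stopping.
- *Three-component MACE and stent thrombosis also need adding.* Section 2.4 already names MACEs among the outcomes to be estimated and plans "comparisons based on narrow versus broader endpoint definitions". Listing stent thrombosis separately is a reporting preference.

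**Conclusion.** The point holds in a limited form. The endpoint list has cardiovascular death as its only general death outcome, and the follow-up text for patients who stop rivaroxaban early contradicts itself on whether a later death has a cause recorded. If the narrower reading was followed, cardiovascular death and the primary composite may be undercounted by roughly 1–2 deaths per 1000. That figure assumes that 10–25% stop evenly over the year, annual mortality of 1.5–2%, constant hazard, and that all affected deaths are cardiovascular. A higher hazard after stopping would raise it; non-cardiovascular causes would lower it. The effect is small for a composite near 5% but not negligible for a death endpoint resting on about 10 events. If the broader reading was followed, the loss may be nil and only the wording needs correction. The remedy is cheap enough to be worth making in either case.

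**What to change.** 1. Reconcile the three statements in Section 2.6. Say which outcomes were collected to one year after rivaroxaban discontinuation, after aspirin discontinuation and after both, and how cause of death was obtained and adjudicated for deaths after the 30-day point.
2. Report all-cause death to one year in all enrolled patients with known vital status, including those who stopped treatment, and give the number with unknown status. Section 2.1 says the manuscript was written after data collection, so label this outcome as added afterwards.
3. Report cardiovascular death and the primary composite twice: with deaths of undetermined cause counted as cardiovascular, and with them not counted. State how many deaths this concerns.

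Cost: a few extra result rows and a post hoc label. Items 2 and 3 need no new data collection. Causes of death that were never recorded may no longer be recoverable, and for those the two-way count gives bounds.
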